### Methods in analysis to handle protocol non-adherence and any statistical methods to handle missing data {20c}

A per-protocol analysis accounting for non-compliance will be performed. Despite this, there is no anticipation of a significant degree of non-adherence and/or missing data, as the intervention will only be carried out during hospitalization and most outcome data after discharge will be generated from the SNQ and DNQD registry. If data is missing from a registry extract, patient records will be searched to complete data collection.

### Plans to give access to the full protocol, participant-level data, and statistical code {31c}

The full study protocol is available upon request. However, participant-level data are not available without ethical approval, in order to protect the patient integrity.

## Oversight and monitoring

### Composition of the coordinating center and trial steering committee {5d}

The main PI for the coordinating center is responsible for overall staff management, including funding and time and resource management.

The main research team consists of the main PI, three senior researchers and one doctoral student responsible for planning, implementation, execution, and analysis of the research. Apart from one, all main researchers are physically located at the coordinating center.

At the coordinating center, there will be a study coordinator with 100% dedication to the project who will help with inclusion and data collection, sampling, biobanking, and overall trial contact managing.

At each university hospital site, there will be at least one study nurse working part-time to manage the inclusion of patients, data collection, and stool sampling. Each site will have a responsible PI who can delegate responsibilities to other clinicians, such as obtaining informed consent. These hospital-site-specific groups will have close day-to-day contact to manage planning of inclusion and other study events, such as stool sampling.

At each satellite hospital site, there will be one main contact and at least one nurse to manage the continuation of the intervention.

The trial steering committee will consist of ten senior neonatologists who are also PIs at each respective hospital. Meetings coordinated by the coordinating center will be arranged at least once per semester during the study and when analyzing and publishing results.

### Composition of the data monitoring committee, its role and reporting structure {21a}

A DSMC was established consisting of two experienced clinicians with expertise in neonatology and research methodology and one biostatistician. All cases of SAEs, SUSARs, and other AEs that clinicians deem concerning and report will be reviewed by the committee. Criteria for stopping the ongoing intervention will be decided by the committee. Information about how SUSARs are reported is described in paragraph below.

### Adverse event reporting and harms {22}

#### Adverse events

AEs are typically defined as unwanted medical events, such as side effects or altered laboratory findings, in a patient who has received the study product—no matter whether it is associated with the intervention given or not. Extremely preterm infants are expected to suffer from various morbidities and may require respiratory support, such as intubation and continuous positive airway pressure (CPAP), for many weeks during the intervention. This will likely influence laboratory findings, such as variations in blood gas tests taken in accordance with standard care. Therefore, medical findings in such tests will not be collected in the eCRF. The same principle applies to other tests as part of standard care, such as an ultrasound, with findings that do not conform to an SAE. If the clinicians are unsure whether to document an AE, this must be discussed with the site PI. Uncertainties about the documentation of AEs can be discussed with main PI and during trial steering committee meetings.

#### Serious adverse events

SAEs are typically defined as unwanted medical events that can result in any of the following outcomes: death, life-threatening medical condition, extended hospitalization, and permanent or significant disability. Extremely preterm infants are vulnerable and at high risk for complications, particularly during the first postnatal weeks. Thus, mortality and various morbidities are expected in the study population. In this trial, we will define expected SAEs as events that occur in over 5% of the study population in accordance with current clinical data from SNQ.

The following SAE are expected in the study population:

Infections; LOS, meningitis, cytomegalovirus (CMV) infectionGastrointestinal; NEC, spontaneous intestinal perforations, volvulus, ileus, other malrotationLung function; bronchopulmonary dysplasia (BPD), respiratory distress syndromeCirculation; patent ductus arteriosus (PDA), pulmonary hypertensionBrain function; intraventricular hemorrhage (IVH), periventricular leukomalacia (PVL), hydrocephalusRetinopathy of prematurity (ROP)Death

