### Probiotics as a nutritional intervention strategy in preterm infants

Despite lack of consensus on methods to prevent NEC, the gut microbiome may work as a preventative target due to the potential to influence the immature gastrointestinal system in extremely preterm infants. In these infants, intestinal bacterial colonization with normal and beneficial bacterial flora (*Bifidobacteria*) is often delayed, rendering the microbiota less diverse and dominated by *Enterobacteriacea*, increasing the potential for the invasion of harmful species [38].

Probiotics are living microorganisms and adequate administration has been linked to numerous benefits, including increased stimulation of immune functions, inhibition of pathogenic bacteria, degradation and fermentation of certain foods, and production of fat-soluble vitamins [39, 40]. The effectiveness of probiotic supplementation in modifying the gut microbiome and preventing NEC and LOS has been shown in recent research; however, the evidence among extremely preterm infants is limited. Further, evidence backing the routine use of probiotics has been challenged due methodological constraints, namely inconsistencies regarding type of probiotics tested, dosage given, enteral feeding routine, intervention duration, outcome measure definition, and general heterogeneity between studies, rendering it difficult to draw sound conclusions on effectiveness [28, 41, 42]. Nevertheless, the recent position paper, “*Probiotics and Preterm Infants*” by the European Society for Paediatric Gastroenterology, Hepatology and Nutrition (ESPGHAN), conditionally recommended probiotic supplementation in infants with birth weight <1500 g if certain safety measures are achieved [15]. The committee recommended providing either *L. rhamnosus GG ATCC53103* or a combination preparation of *Bifidobaterium infantis Bb-02*, *Bifidobacterium lactis Bb-12*, and *Streptococcus Thermophilus TH4*, the latter of which will be used in our study.

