## Interventions

### Choice of probiotic {6b}

The PEPS trial will us the probiotic supplement known commercially as ProPrems®, which is comprised of a combination of one billion freeze-dried bacteria per 0.5 g in a maltodextrin base powder (*Bifidobacterium infantis Bb-02* (DSM 33361) 300 million, *Bifidobacterium lactis* (BB-12®) 350 million, and *Streptococcus thermophilus* (TH-4®) 350 million). The probiotic supplement is one of two probiotic combinations recommended by the ESPGHAN committee [15]. The product is produced by Chr Hansen in Denmark and distributed by the Swedish company Neobiomics©. The product is currently being used routinely in all Swedish hospitals for infants born in gestational weeks 28 to 32. Thus, the PEPS trial will be easy to implement considering the product is already familiar to medical and nursing staff at the participating hospitals. However, participating Danish hospitals have not implemented any probiotic supplement into clinical routine and will need to learn these routines. The control group will receive placebo produced by Chr Hansen containing 0.5 g maltodextrin powder, equivalent to the amount of maltodextrin included in the probiotic supplement.

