#### Diagnostic/validation of LOS

LOS is defined as culture-proven sepsis via blood and/or urine culture and/or significant clinical impairment and laboratory inflammatory response, where at least one of the following must be confirmed:Leucocytes (LPK) < 5 or > 20 (×10^9^ cells/L)Thrombocytes (TPK) < 100 (×10^9^ cells/L)C-reactive protein (CRP) > 15 mg/L

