#### Reporting serious adverse events

All SAEs will be recorded in the eCRF and do not need to be documented immediately. However, to be able to carry out interim analyses, all SAEs must be documented no later than 2 weeks after the intervention has ended for each patient.

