#### Suspected unexpected serious adverse events

SUSARs are typically defined as a reaction or event that is unexpected, serious, and suspected to be caused by the intervention. In this trial, death is defined as an SAE. However, when a SUSAR occurs in connection to an event that later causes death, this must be reported.

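### The 5% rule and the list of expected SAEs conflict for infection with an administered strain; read by the list, such a case misses the 24-hour SUSAR route

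*Protocol article*

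**What the plan says.** All places are in the protocol article.

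- **Expectedness.** Serious adverse events, under {22}, gives the rule: "we will define expected SAEs as events that occur in over 5% of the study population in accordance with current clinical data from SNQ". A list by organ system follows. Its infection entry begins "Infections; LOS, meningitis, cytomegalovirus (CMV", and NEC and death are also on it. No entry is limited by organism, cause or suspected relation to the product.
- **SUSAR.** Suspected unexpected serious adverse events requires "a reaction or event that is unexpected, serious, and suspected to be caused by the intervention". The same section classes death as an SAE, but requires reporting when a SUSAR is connected to an event that later proves fatal.
- **Fast route.** Reporting SUSARs asks for a telephone report to the main PI within 24 hours. Management and follow-up of SUSAR has the main PI inform the DSMC immediately.
- **Slow route.** Reporting serious adverse events says "All SAEs will be recorded in the eCRF and do not need to be documented immediately". The deadline is two weeks after the end of the intervention, set so that interim analyses can be run.
- **LOS.** Diagnostic/validation of LOS states: "LOS is defined as culture-proven sepsis via blood and/or urine culture and/or significant clinical impairment and laboratory inflammatory response". No organism is excluded.
- **Product.** Choice of probiotic {6b} describes "one billion freeze-dried bacteria per 0.5 g in a maltodextrin base powder", from three named strains. The introduction notes that "Probiotics are living microorganisms".
- **Other safeguards.** Under {21a} the DSMC reviews all SAEs. Table 1 records the type of pathogen for culture-proven LOS.

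**The concern.** How often sepsis occurs in this population does not tell us whether sepsis caused by the administered organism is expected. The registry rate describes background infection. An isolate of a study strain from blood or CSF would be a specific harm of the product. The introduction describes these infants as having immature mucosal barriers and immature immune responses, so this is a harm the reporting rules should handle clearly.

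The list works by diagnosis, and only unexpected events reach the fast route. The most product-specific infectious harm can therefore be filed with ordinary background sepsis. What is at stake is how soon the DSMC learns of it.

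**Working it through.** No sample size, power or alpha figure bears on this point, so there is no figure of the plan to reproduce. The check follows one case through the stated rules and then does date arithmetic on the two reporting clocks.

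**Case: blood culture grows an administered strain, and the investigator suspects the product.**

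1. The event is culture-proven sepsis. The LOS definition excludes no organism, so it is LOS.
2. LOS is on the expected list without qualification. Read by the list, the event is expected.
3. A SUSAR must be unexpected. The event is serious and suspected to be caused by the product, but fails this condition.
4. The 24-hour telephone report and the immediate DSMC notice apply to SUSARs, so neither is triggered.
5. The ordinary SAE deadline applies.

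The same steps hold for a CSF isolate, through the meningitis entry.

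**The other reading.** If the 5% rule is applied to the specific event (sepsis with a study strain) rather than to the diagnosis, nothing in the article shows that it exceeds 5%. The event would be unexpected and step 3 would make it a SUSAR. Rule and list give opposite answers for one case.

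**Latest permitted documentation date.** Inputs: gestational age at birth 22+0 to 27+6 (Study setting {9}); intervention until 34 weeks (Intervention description {11a}); two further weeks (Reporting serious adverse events).

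- Formula: days after birth = (34 weeks in days − gestational age at birth in days) + 14.
- 34+0 = 34 × 7 = 238 days.
- Born at 22+0 = 154 days: (238 − 154) + 14 = 84 + 14 = 98 days.
- Born at 27+6 = 27 × 7 + 6 = 195 days: (238 − 195) + 14 = 43 + 14 = 57 days.
- The permitted delay is these figures less the time from birth to onset. The introduction places LOS after the first 72 hours, so for LOS the ceilings are 98 − 3 = 95 and 57 − 3 = 54 days. They fall further because dosing starts only once 3 mL per meal is tolerated.
- If the infant dies during the intervention, it ends at death and the limit is 14 days.

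The SUSAR clock is 24 hours.

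**Death.** The provision on death acts only where a SUSAR exists. If an unlisted, suspected-related event precedes the death, that SUSAR is reported. If the preceding event is itself listed (LOS or NEC, for example), or death is the only event, then on the list reading there is no SUSAR for the provision to act on.

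**The case against.** - **The event-level reading is available.** An investigator could apply the 5% rule to the specific infection and report a SUSAR. This stands, and it is why the point is a conflict between rule and list. It would go too far to say that such a case is certainly excluded. Still, the list is what a site will consult, and it names diagnoses without organisms.
- **The DSMC sees every SAE, and pathogen type is recorded.** This also stands. A reader might infer that a product-strain case would be lost among ordinary LOS cases in a comparison of totals. Case-level review under {21a} means that detection need not depend on such a comparison. What remains is timing, since neither safeguard has a time limit.
- **Death is partly covered.** A reader might infer that any death suspected to be product-related avoids fast reporting. The provision on death prevents that general claim; only the two situations shown in the working remain.
- **The delays are ceilings.** They are latest permitted dates, and sites may well enter events sooner.
- **The article condenses a fuller protocol.** That protocol is available on request, and a dedicated REDCap form for SUSARs is mentioned. Causality assessment may be set out there. But the conflict lies in rules the article itself states, not in missing detail.
- **The list might seem to break its own 5% criterion.** A reader might doubt that meningitis, CMV infection or volvulus each exceed 5% (0.05 × 1620 = 81 infants). The article gives no SNQ rate for them, so no breach can be shown and none is claimed.

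**Conclusion.** The point holds as an internal conflict with a safety consequence. By the list, serious infection with an administered strain is expected and goes by the slow route. By the 5% rule at event level, it is unexpected and goes by the 24-hour route.

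On the list reading, documentation may lawfully wait until 57 to 98 days after birth, depending on gestational age at birth and less the time to onset, or 14 days after a death during the intervention. These figures assume that the intervention runs to 34+0 in survivors and ends at death otherwise.

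The event is still recorded and reviewed; what is lost is the fast route. The documents give no rate of product-strain infection and no LOS rate, so the number of infants affected cannot be estimated from them, and the verdict does not depend on it.

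**What to change.** Reconcile the expected list, the SUSAR definition and the two reporting sections under {22}, so that background frequency does not decide expectedness for an event suspected to be caused by the product. In particular:

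1. State that an isolate of an administered species from blood or CSF is not an expected SAE, and that it goes by the 24-hour route to the main PI and on to the DSMC.
2. Have the site report on the culture result. The LOS pathogen variable in Table 1 should not be the trigger: {18a} draws outcomes mainly from registries, the eCRF variables printed there do not include pathogen, and the LOS definition names blood and urine cultures but not CSF.
3. State how a listed event, including death, is classified and reported when the investigator suspects the product.
4. Keep any code break arising from these reports within the DSMC. Section {11b} ties code breaking to SUSARs, and {16b} uses only two codes, C and D, at all hospitals. Decoding one infant would reveal the whole allocation to whoever learns it. Emergency unblinding under {17b} is a separate matter.

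The cost is a wording change, which may need handling as an amendment under {25}, and a few extra expedited reports. Some may prove unrelated, because a species match does not establish that the isolate is the product strain.

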#### Reporting serious adverse events

All SAEs will be recorded in the eCRF and do not need to be documented immediately. However, to be able to carry out interim analyses, all SAEs must be documented no later than 2 weeks after the intervention has ended for each patient.

#### Suspected unexpected serious adverse events

SUSARs are typically defined as a reaction or event that is unexpected, serious, and suspected to be caused by the intervention. In this trial, death is defined as an SAE. However, when a SUSAR occurs in connection to an event that later causes death, this must be reported.

#### Reporting SUSARs

Investigators are required to report SUSARs to the main PI as soon as possible and no later than 24 h following the incident. The initial report must be made by phone.

A complementary written report must be completed immediately using the data collection instrument in REDCap entitled, “reporting of SUSAR.”

In the event of code breaking in connection to a SUSAR, blinding must still be preserved during the ongoing trial. The oral or written report should therefore not contain information about regarding whether the patient was receiving the probiotic supplement or not.

#### Management and follow-up of SUSAR

The main PI at Karolinska University Hospital will oversee the reporting of SUSARs to the DSMC immediately after receiving the report. The DSMC will also have accesses to the written report in REDCap. The DSMC will investigate and follow-up all SUSAR events.

### Frequency and plans for auditing trial conduct {23}

As most data collection is registry-based, the need for auditing trial conduct regarding quality of data collection is limited. As such, auditing of trial conduct will not be undergone. The main research group will have access to all data collection made at all hospitals in REDCap. Site monitoring will thus mainly be made by auditing data collection, such as missing variables, in REDCap. Potential need for revision of trial conduct will mainly be handled by the trial steering committee meeting.

### Plans for communicating important protocol amendments to relevant parties (e.g., trial participants, ethical committees) {25}

The main PI and the study coordinator will be responsible for communicating any relevant amendments to the study protocol to all relevant parties. All protocols will be dated and version managed. Potential amendments to the study protocol will also be documented in a separate report file to ease the identification of alterations. If any major changes are made to the study protocol, an amendment will be sent to the Swedish Ethical Review Authority and the Danish Ethical Review Authority if applicable (complete cohort).

### Dissemination plans {31a}

The main PI is responsible for finalizing the study report. The results will be published in scientific peer-reviewed journals and presented at national and international congresses and scientific meetings.

## Discussion

To our knowledge, the PEPS trial is the first sufficiently powered, placebo-controlled RCT evaluating the effect of probiotic supplementation in preventing NEC, total mortality, and other secondary and tertiary endpoints in extremely preterm infants. The results will provide high-quality evidence and likely inform supplementation recommendations in this population. Furthermore, this trial may also add new knowledge on the effect of probiotic supplementation on feeding tolerance and growth, microbiome diversity and development, and body composition in relation to nutritional intake. We believe these results will provide important in-depth knowledge in the context of the results from the main trial.

Despite extensive undertaking of probiotic trials in preterm infants, many challenges have been encountered. Firstly, these trials have often been small in scale and underpowered to effectively evaluate efficacy among extremely preterm infants. Additionally, there has been inconsistency in the selection of outcomes and study populations, rendering studies incomparable. Any combined analyses of these trials have further been limited by their heterogeneity due to considerable variation in investigated probiotic strains and dosages, rendering it difficult to draw clear conclusions [17]. This knowledge gap is especially notable in the case of extremely preterm infants, who are at the highest risk for conditions, such as NEC, sepsis, and mortality. While studies have frequently involved this group of patients, they often fail to specifically examine the effects of probiotics in this population. As a result, there is frequently an inadequate number of patients included and inconclusive groups from the resulting subgroup analysis.

A recent systematic review and meta-analysis of 60 trials with data on 11,156 infants found a 46% lower risk of NEC and 23% lower risk of mortality among very preterm or low birth weight infants following probiotic supplementation [43]. However, these comparisons only provided low or moderate certainty of evidence and the corresponding estimates for extremely preterm or extremely low birth weight infants were not statistically significant for NEC and total mortality. The review further underlined the need for large, high-quality trials, particularly for this population of extremely preterm infants.

Although the prominent ProPrems trial conducted on infants born <32 weeks of gestational age reported a 54% reduced risk of NEC of Bell stage II or more following provision of the combination preparation of *B. infantis Bb-02*, *B. lactis Bb-12*, and *Str. thermophilus TH4*, this trial was underpowered for extremely preterm infants [12]. Nevertheless, the 2020 ESPGHAN position paper concluded that either *L. rhamnosus GG ATCC53103* or the combination of *B. infantis Bb-02*, *B. lactis Bb-12*, and *Str. thermophilus TH4* used in the ProPrems trial can be given to infants with birth weight <1500 g, which strengthens the investigation of this product in our study population [15]. Despite national uncertainty regarding the efficacy of probiotics in extremely preterm infants, the high incidence of NEC and mortality warrants the need for future research. Through providing sufficiently powered, high-quality evidence on the potential effectiveness of probiotic supplementation in extremely preterm infants, the results of this study will have implications on both national and international guideline development and clinical practice, thereby strengthening the evidence-based care of this vulnerable patient population going forward.

